### Criteria for discontinuing or modifying allocated interventions {11b}

Participants are able to discontinue the study intervention at any time without giving reasons and without suffering any disadvantage, as stated to them prior to informed consent. The study intervention will be discontinued, if it becomes apparent that the system requirements for using the DiGA are not met. Furthermore, study intervention (seeking contact through the digital nurse) will be stopped, if it becomes apparent that the patient's mental or somatic health has deteriorated significantly, and the patient is currently unable to use the DiGA.

When a subject discontinues from the study intervention but not from the study, the remaining study assessments will be completed as indicated by the study protocol.

The data to be collected at the time of study intervention discontinuation will include the following:Point in timeThe reason(s) for discontinuing the intervention.If possible, the primary endpoint and depressive symptoms at the time of discontinuation.

Thereafter, the participant will be included in all future scheduled assessments, even though not participating in the intervention.

### Strategies to improve adherence to interventions {11c}

During the intervention phase, there are no restrictions on the number, duration, or type of contacts (telephone, videocall, face to face). The meetings are deliberately organized according to the patients’ needs in order to improve adherence. However, the digital nurse will contact the patient at least once a week at the beginning of the intervention period.

The mode of administration, number, and total support time for each participant will be documented and evaluated.

### Relevant concomitant care permitted or prohibited during the trial {11d}

Since DiGA can be used as an add-on therapy to the best medical care, all concomitant therapies are allowed. As the secondary endpoint of depressive symptoms (PHQ-9) might be influenced by concomitant psychotherapies or the use of antidepressants, the number and/or dose of these therapies is recorded.

### Provisions for post-trial care {30}

The possibility to use the prescribed DiGA does not end at the end of the follow-up period. The DiGA may be used by the patients as long as desired. If they wish to use the DiGA for longer than the intended duration of use (prescription valid for 90 days), patients must obtain a follow-up prescription themselves. Participating patients also have the opportunity to contact the clinics and practices after their participation in the study has ended.

### Outcomes {12}

The primary endpoint is DiGA use at week eight after randomization (yes/no). It is recorded whether the patients have started using the DiGA within 8 weeks, i.e., whether they have started at least the first online session. We chose an intervention period of 8 weeks because administrative processes such as request to the health insurance companies, and the installation/navigation to the website may last several weeks until the first use of the DiGA is possible at all.

Secondary endpoints are DiGA use after 16 weeks, change in depressive symptoms (measured by PHQ-9 [26]), and change in treatment of mental disorder after 8 and 16 weeks. The usability of the DiGA will be assessed by the System Usability Scale (SUS) [27] and the User Experience Questionnaire (UEQ) [28] at week eight and 16.

All outcomes will be assessed via personal/telephone interviews and patient self-report.

### Participant timeline {13}

The participant timeline is shown in the table below [26–31].

**Table Tabb:**
[figure not shown]

*If organizationally possible, **is only asked again if the baseline assessment is scheduled on a different day than the patient's inclusion to the study. Otherwise, suicidality is already queried during the enrolment process

### Sample size {14}

The sample size to test the main hypothesis was calculated using a Fisher’s exact test at a one-sided significance level of 5% and to achieve a power of 80%. It was assumed that under control 30% of the participants would start using DiGA and that this proportion would be increased to 50% through the support of the digital nurse. This resulted in a required number of cases of 84 patients per group. Due to a possible drop-out (assumption approx. 15%), 100 patients per group should be included in the study.

### Recruitment {15}

Recruitment will take place at all three participating hospitals (see 9.), as well as at selected primary care practices. For recruitment in the participating hospitals, patients can be recruited from the outpatient clinic, the ward, and the day clinic. Due to different populations and settings, recruitment procedures will differ between hospitals and primary care practices, inpatient and outpatient settings in hospitals, and even between the participating hospitals themselves. Recruitment should fit as well as possible into the respective clinic’s and practice’s daily routine to ensure feasibility and success. The procedure described below will therefore be adapted to the conditions in the respective setting, and screening manuals will be written.

#### General recruitment procedure

##### Step 1: eligibility screening

Patients will be recruited as they visit the clinic (inpatient or outpatient) or practice. First, patients are screened regarding age. Those aged ≥ 60 years are further screened with regard to mild or moderate depression based on ICD-10 codes F32.0, F32.1, F33.0, and F33.1. No restrictions about gender, race and ethnicity, or upper age limit are made. However, in order to use all survey instruments, a restriction to sufficient German language skills is necessary. Thus, sufficient knowledge of the German language and the ability to give informed consent is judged. These patients are invited to participate in the study and the final eligibility screening.

##### Step 2: final eligibility screening

Depending on the recruitment setting eligible patients are approached by the general practitioner (GP)/clinician or study nurse for final eligibility assessment. If a patient is eligible according to all criteria mentioned above, the patient is invited to participate in the study and receives the DiGA prescription. After the provision of written informed consent (see item 26a above), participants are then randomized to the intervention and control group. If necessary, a new appointment to start the intervention is made.

##### Step 3: start of intervention

The intervention starts with a short information film. Participants of the intervention group additionally have their first appointment with the digital nurse afterwards.

## Assignment of interventions: allocation

### Sequence generation {16a}

To guarantee adequate sequence generation and allocation concealment, centralized online randomization with 1:1 allocation to intervention or control group is done through REDCap. Permuted blocks of random length are used and are stratified by the center to guarantee nearly equal group size within each center.

### Concealment mechanism {16b}

Allocation concealment will be ensured, as the software will not release the randomization code until the patient has been entered into the trial, which takes place after all baseline measurements have been completed.

### Implementation {16c}

A person at the Department of Medical Informatics, Biometry, and Epidemiology (AMIB) not further involved in the study creates the allocation sequence which will be implemented in REDCap; clinicians and study nurses will enroll participants and will assign them to the interventions accordingly.

## Assignment of interventions: blinding

### Who will be blinded {17a}

It is not feasible nor possible for the participating patients and most project staff to be blinded to treatment allocation. Primary outcome assessment will be based on patient report, blinding is not possible. Staff who analyze the data will be blinded (arms will be designated randomly at that point as A and B). Data review will be performed blinded.

### Procedure for unblinding if needed {17b}

The trial design is open-label, and therefore, there is no unblinding procedure.

## Data collection and management

### Plans for assessment and collection of outcomes {18a}

Data collection will be the responsibility of the clinical trial staff under the supervision of the site investigator. The investigator will be responsible for ensuring the accuracy, completeness, legibility, and timeliness of the data reported.

In accordance with the clinical routine, study visits will take place on-site at the clinic or practice, study data will be captured on printed Case Record Forms (CRF), and then entered in the corresponding electronic (e)CRF as soon as possible or captured directly through the eCRF (see the “Data Management {19}” section). Patient questionnaires will be filled out during the waiting times of the visits. Most questionnaires used are validated (see the “Outcomes {12}” section). Prior to the start of the study, the leading site investigator will instruct all study personnel on study procedures and the study-related data collection process.

The diagnosis of depression, possible bipolar disorder, schizophrenia, moderate or severe dementia, or other severe psychiatric disorders (exclusion criteria) is made by the treating physician or psychotherapist. The assessment of cognitive performance (MOCA) is made by the treating physician or psychotherapist and/or trained study nurse as far as this is possible in the course of medical care. It is to be expected that MOCA will be collected in inpatient clinics in particular. The assessment of German language skills and possible auditory and/or visual impairments will be made by the recruiting physician at his/her own discretion. The patient is asked about comorbidities, including terminal illness, current or former use of a prescribed depression DiGA, and participation in other studies.

After inclusion in the study, baseline data and baseline questionnaires are collected. Patient-reported data is collected via an online survey using a tablet or by face to face interviews by the study personnel. The assessments after 8 and 16 weeks are not planned at present as all outcomes are purely self-reported by the patients. These data will be collected via telephone interviews with the study personnel or via an online survey.

The information of the support provided by the nurse will also be collected as part of the study and will form the basis for the development of a standardized support concept by the digital nurse, which will then be investigated in multi-center studies.

### Plans to promote participant retention and complete follow-up {18b}

At study inclusion, patients can choose their mode of follow-up assessments. They can choose between contact by the study personnel to assess data via interview or getting a link to the eCRF on their mailing address. If a participant chooses the second option but does not complete the eCRF within the timeframe provided, the center will contact the participant by telephone and offer help and counseling to finish the assessment.

If a patient misses one scheduled assessment, the following actions must then be taken:The site will attempt to contact the participant, within 1 week, counsel the participant on the importance of maintaining the assigned assessments and, if possible, will perform the assessment by telephone. Furthermore, the site will ascertain if the participant wishes to continue in the study.Before a participant is deemed lost to follow-up, the investigator or designee will make every effort to regain contact with the participant (where possible, five telephone calls, or three calls, and two certified letters to the participant’s last known mailing address). These contact attempts will be documented in the participant’s medical record or study file.Should the participant continue to be unreachable, he or she will be considered to have withdrawn from the study with a primary reason of lost to follow-up.

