#### Safety analysis dataset

The safety analysis set will include all randomized patients.

Missing values of the primary endpoint will be imputed. Details of the model, imputation of missing values and sensitivity analysis will be specified in the SAP.

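### A patient unreachable after one missed assessment is classed as withdrawn, and nothing provides for a week-16 contact that could still settle the week-8 primary endpoint

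*Protocol article*

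**What the plan says.** After baseline there are two outcome time points, weeks 8 and 16 (sections {12} and {18a}). The retention rule in {18b} starts from a single failure: "If a patient misses one scheduled assessment, the following actions must then be taken". The site tries to reach the patient within a week and, if possible, does the assessment by telephone. Before declaring loss to follow-up it makes a defined effort: "where possible, five telephone calls, or three calls, and two certified letters to the participant’s last known mailing address". If that fails: "Should the participant continue to be unreachable, he or she will be considered to have withdrawn from the study". The reason is recorded as lost to follow-up. The rule does not treat week 8 differently from week 16.

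On the primary endpoint, {12} says: "It is recorded whether the patients have started using the DiGA within 8 weeks". The source is the patient, as {17a} confirms: "Primary outcome assessment will be based on patient report, blinding is not possible". The same question returns later: "Secondary endpoints are DiGA use after 16 weeks". For gaps, {20c} says: "Missing values of the primary endpoint will be imputed". It leaves the method to the SAP.

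Section {11b} deals with patients who stop the intervention but stay in the study: "Thereafter, the participant will be included in all future scheduled assessments, even though not participating in the intervention".

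**The concern.** Many endpoints are lost if they are not measured on the day. This one is not. Whether a first session took place within 8 weeks of randomisation does not change afterwards, and the patient can still report it at week 16. The trial already schedules a contact at that time and already asks about use.

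The rule in {18b} does not separate a patient who could not be found around week 8 from one who has decided to leave. Both end up as withdrawn from the study. A site that applies the rule literally would have no reason to try again at week 16. The missing primary value would then be imputed although one further call might have supplied it. The patient's week-16 outcomes would be missing too, and {20a} analyses secondary outcomes on complete cases. An SAP can choose how to impute, but it cannot restore an answer that nobody asked for.

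**Working it through.** **1. Which patients are promised a week-16 assessment?**
- Stopped the intervention but not the study: yes, by {11b}.
- Withdrew consent: no further data are collected, by {27}.
- Missed week 8 and still unreachable after the effort in {18b}: classed as withdrawn from the study. This takes them outside the promise in {11b}. They have not withdrawn consent, so the stop in {27} does not apply either. No section says that week 16 is attempted, and none says that it is cancelled.

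**2. What would a week-16 answer settle?** For a patient with no week-8 value:
- Never started: week-8 value is 'no', by logic and without a date.
- Started, dated within 8 weeks of randomisation: 'yes'.
- Started, dated later: 'no'.
- Started, date unknown: still open.
- Not reached again: still open.

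Only the last two groups need imputation.

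**3. The plan's own sample size.** Inputs from {14}: 30% versus 50%, one-sided Fisher's exact test at 5%, power 80%, drop-out about 15%; 1:1 allocation from {16a}. Exact power is the sum over all pairs (c, i) of Bin(c; n, 0.30) × Bin(i; n, 0.50), counting the pairs for which the one-sided hypergeometric p-value is at most 0.05.
- n = 83 per arm: 0.798
- n = 84 per arm: 0.805

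So 84 is reproduced. Inflation: 84 / (1 − 0.15) = 98.8, which gives 99; the plan rounds to 100.

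**4. The ceiling.** 0.15 × 200 = 30 patients, 15 per arm. This takes all assumed drop-out to be patients unreachable at week 8. The true number is smaller if some of them withdraw consent or are lost only at week 16.

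**5. Effect on power.** Let r be the share of the 15 per arm recovered at week 16, so that n is about 85 + 15r. The documents give no value for r, so the whole range is shown:

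| r (assumed) | n per arm | exact power |
|---|---|---|
| 0 | 85 | 0.811 |
| 0.1 | 86 | 0.818 |
| 0.2 | 88 | 0.832 |
| 0.5 | 92 | 0.845 |
| 1 | 100 | 0.867 |

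These figures use the planning test on observed cases. The planned analysis is a covariate-adjusted logistic regression with imputation, so they indicate size only.

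**The case against.** The strongest reply is that {18b} assigns a status and does not forbid a call. It applies only after repeated attempts, and data collection is expressly stopped only when consent is withdrawn ({27}). No closing date is given for the attempts, so a patient missed at week 8 might still be under re-contact at week 16. This stands against the stronger reading that the week-16 contact is never made. That is the natural inference from being withdrawn from the study, but the text does not say it. What remains is that the contact is not provided for.

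Three further inferences are tempting and not supported.
- **Loss differs by arm, because the nurse stays available until week 16 in one arm only.** The rule in {18b} is the same for both arms and is carried out by the site. Under {11a} the nurse is then available for problems or questions, and nothing links this to outcome collection.
- **Late, undated replies count starts after the window.** The recorded item in {12} is tied to 8 weeks. Whether the form also asks for a date cannot be seen from an article.
- **A particular number of endpoints would be recovered or misclassified.** This needs a recovery share and a pattern of start times that the documents do not give. A constant start rate would also fit poorly with {12}, which expects administrative steps to take up to several weeks before first use is possible.

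It is also fair to say that deriving the endpoint and imputing it are SAP matters. Whether the patient is contacted is not: it is a rule of conduct, and it is fixed in {18b}.

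**Conclusion.** The point holds as a weakness in data completeness, not as a numerical error. As written, {18b} turns one missed assessment followed by failed contact into withdrawal from the study, and the article does not provide for using the week-16 contact to settle the week-8 endpoint. Some observable primary values may be imputed as a result. Their number is unknown; about 30 of 200 is an upper limit that rests on the plan's 15% and on all of that loss occurring at week 8. The sample size already allows for this loss, so power stays at about 0.81 even if nobody is recovered. The gain from a change is less reliance on imputation for the primary endpoint. It is worth making because it is cheap and cannot be made good after the data are in.

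**What to change.** In {18b}, record a patient who cannot be reached at week 8 as 'week-8 assessment missed', and keep withdrawal for those who withdraw. State that the week-16 assessment is attempted for everyone who has not withdrawn consent. At week 16, ask whether the first session has been started and, if so, on what date, unless the form already does so. In the SAP, when week 8 is missing, set the primary endpoint from a week-16 report of never having started or from a dated start, and impute only what is still unknown.

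Cost: a sentence or two in {18b}, at most one date field, and no new visits. The downsides are a few more calls to patients already missed once, and a start date recalled at week 16 that is less exact than one given at week 8.

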### Data management {19}

The clinical trial staff at the participating centers under the supervision of the site investigator will be responsible for data entry. The investigator will be responsible for ensuring the accuracy, completeness, and timeliness of the data reported. All source documents will be completed in a neat, legible manner to ensure accurate interpretation of data. Clinical data will be entered into REDCap (Research Electronic Data Capture), a system provided by the AMIB [32, 33]. REDCap is a secure, web-based software platform designed to support data capture for research studies. It provides 1) an intuitive interface for validated data capture; 2) audit trails for tracking data changes and exports; 3) automated export procedures for seamless data downloads into common statistical packages; and 4) procedures for data integration and interoperability with external sources. The data system provides internal quality checks, such as automatic range checks, to identify data that appear inconsistent, incomplete, or inaccurate. Prior to the start of recruitment, the staff in the clinics and practices involved in this study receives training regarding data entry and management using REDCap.

Data capture and processing will be in accordance with the applicable law on personal data protection and with the GDPR (EC) 2016/679 of the European Parliament and of the council. Access to the data is strictly limited to authorized persons. Data are protected against unauthorized access. The database is hosted by the AMIB on servers, which are located at the RUB in access-protected server rooms.

Personal data collected for this study will be stored for 10 years from the completion of the study. When the study is completed, access to study data will be provided upon request to the PI.

### Confidentiality {27}

All data will be initially collected by investigators in the recruiting trial sites. Together with information on the trial, eligible patients will be informed about data capture, transmission, analysis processes, and their rights according to the General Data Protection Regulation (GDPR). Once a patient is eligible and has given his/her informed consent (concise version) to trial participation and data collection, the investigator will assign with the help of a separate “contact database” the patient a unique patient identification code. Patient identification code lists will be filled at the recruiting sites, and are part of the investigator site file. These lists are the only documents that allow for re-identification of the patients and remain at the recruiting site. Access is only possible for authorized persons of the study team. All clinical data entered by the investigators (or their designated staff) into eCRFs will be recorded in an anonymized form exclusively using the patient’s identification code.

Patients may withdraw their informed consent. If patients withdraw their consent, no further data will be collected. However, the data processing carried out up to the date of withdrawal remains lawful. If the informed consent is withdrawn, the patient has the right of data deletion according to the GDPR. Information as to when and why a patient was randomized and when he withdrew consent must be retained in the documentation. According to GDPR, the institution responsible for conducting the study is generally obliged to delete its data from the study database after the withdrawal of consent.

### Plans for collection, laboratory evaluation, and storage of biological specimens for genetic or molecular analysis in this trial/future use {33}

Not applicable.

## Statistical methods

### Statistical methods for primary and secondary outcomes {20a}

We assume that the additional support from a digital nurse will lead to a greater proportion of older patients using the DiGA compared to support from an explain film alone.

Since this is a feasibility and proof-of-concept study, the main hypothesis will be tested one-sided at a significance level of 5%, i.e., the null hypothesis “smaller or equal frequency of use in the intervention group compared to the control group” vs. the alternative hypothesis “greater frequency of use in the intervention group compared to the control group” will be tested, i.e., the following null and alternative hypothesis will be tested:$$H_0:p_I\leq p_{K\;}vs.\;H_1:p_I>p_K.$$

Here, $${p}_{I}$$ and $${p}_{K}$$ stand for the frequency of DiGA use in the intervention (digital nurse) and control group, respectively.

